### Sample Size

A minimum efficacy of 30% was set, and efficacy of 60% is expected to be achieved [14]. The hypotheses tested are P≤0.30 (H0) and P≥0.60 (H1), where P corresponds to the rate of patients with disease control at 3 months. Based on an optimal 2-step Simon plan (5% unilateral test), a total of 24 patients is required to test these hypotheses with a power of 80%: 8 patients are included in a first step, and the trial is stopped if the number of patients with a disease control at 3 months is less than or equal to 3; the PAGETEX device is considered not sufficiently effective. Otherwise, 16 additional patients are included in a second step. The PAGETEX device is not considered sufficiently effective if, on the 24 patients included (step 1 + step 2), the number of patients with a disease control at 3 months is less than or equal to 10.

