### Implementation and Blinding

The study is not concerned with blinding as it is an uncontrolled clinical trial on a single group of patients receiving the same PDT treatment. However, to minimize the bias of investigator evaluation, an independent medical committee will evaluate the type of clinical response (stable, partial, complete, or no response) obtained at 3 and 6 months from standardized lesion photographs. Data will also be analyzed without blinding.

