To answer to the main objective, the rejection rules of Simon’s optimal plan will be used. According to Simon’s optimal plan, after including 8 patients in a first step, the experimental treatment (PDT treatment with the PAGETEX device) will be rejected if the number of patients with disease control at 3 months (assessed by the investigator) is less than or equal to 3. If the trial continues in the second stage, the experimental treatment will be rejected if, out of the 24 patients, the number of patients with disease control at 3 months is less than or equal to 10. The 95% bilateral confidence interval of the 3-month disease control rate will be calculated. The control rates of the disease and its 95% confidence interval, as assessed by the investigating physician and the independent committee, will be calculated. Changes in the quality of life, sexual quality of life, anxiety, and depression measured by the DLQI, HADS, FSFI, and SF-36 questionnaires will be estimated using a mixed linear model (covariance pattern ) including time (inclusion visit, visit at 3 months, visit at 6 months) as the fixed effect. The pain experienced measured by the visual analog scale will be described as a continuous variable and as a qualitative variable to 4 classes. Severity of the erythema assessed by a 4-point ordinal scale will be described at each time (inclusion, 3 months, and 6 months). Severity of the erythema evaluated at follow-up visits will be compared to severity of the erythema evaluated at the inclusion visit using the Wilcoxon signed-rank test. Percentages of patients with a decrease in severity grade at 3 months and 6 months compared with baseline will be described. Evolution of the severity of the erythema quantified by a colorimetry will be evaluated by the same method. The presence of fluorescence in Paget cells after each PDT session will be described to prove the production of PpIX. The link between the presence of fluorescence after each PDT session and the disease control rates at 3 months and 6 months will be studied using a Fisher exact test. Finally, rates of patients with at least one Paget cell in the thickness of the epidermis biopsies, patient satisfaction questionnaires scores, and frequencies of adverse events will be described.

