## Discussion

PDT using 5-aminolevulinic acid has been employed sporadically to treat EMPV even if it is not the common treatment of this pathology [15,16]. MAL-PDT is a relatively simple procedure to treat large and multiple lesions and can be repeated without functional or cosmetics effects. This clinical trial is the only trial registered on ClinicalTrials.gov that investigates the efficacy and safety of PDT in EMPV. But its boundaries are that disease evolution is difficult to evaluate because symptom improvement is based on a medical opinion by comparison of photographs and the limitation of the penetration of MAL at a depth of around 2 to 3 mm for a wavelength of 630 nm according to the thickness of the lesions. In case of positive results, a randomized trial comparing PDT with imiquimod will be performed.

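### The Simon go/no-go rules count the investigator's open rating, while the committee added to limit investigator bias decides neither step

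*Protocol article*

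**What the plan says.** All references are to the protocol article.

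- **Sample Size** sets the test without naming a rater: "The hypotheses tested are P≤0.30 (H0) and P≥0.60 (H1), where P corresponds to the rate of patients with disease control at 3 months". The design is 8 patients, stopping at 3 or fewer controlled, then 16 more, with rejection at 10 or fewer of 24.
- **Statistical Methods** makes these rules the answer to the main objective and names the rater for step 1: "number of patients with disease control at 3 months (assessed by the investigator) is less than or equal to 3". The step 2 sentence does not repeat the rater.
- **Implementation and Blinding** gives the committee its purpose: "to minimize the bias of investigator evaluation, an independent medical committee will evaluate the type of clinical response". It does so at 3 and 6 months, from standardized photographs.
- **Table 1** and **Preparation and Treatment of Lesions** call the committee blinded and have both raters judge the lesion. Table 1 lists the two together under primary outcomes.
- **Statistical Methods** uses the committee's rating once: "The control rates of the disease and its 95% confidence interval, as assessed by the investigating physician and the independent committee, will be calculated".
- **Discussion** concedes that the assessment is subjective: "symptom improvement is based on a medical opinion by comparison of photographs".

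**The concern.** The protocol identifies a bias and sets up a remedy for it, then takes the decision on the rating that the remedy was meant to guard against. The committee's classification is reported beside the investigator's. It does not decide whether step 2 opens or whether the device is judged sufficiently effective, and nothing says what follows if the two ratings fall on opposite sides of a cut-off.

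This trial is sensitive to that choice. There is one arm, and assessment in person is open. Disease control includes stability, so success turns on the line between stable and not controlled, which leaves much to judgement. The counts are small: one patient moved across that line turns 3 of 8 into 4 of 8 and opens step 2.

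**Working it through.** **1. Who feeds each rule.** Step 1 names the investigator explicitly. Step 2 counts the same end point over all 24 patients, including the first 8. A cumulative count that changed rater between steps would not be coherent, so the investigator's rating is the only consistent reading, but it is an inference. Sample Size names no rater and Table 1 names both. No section gives the committee a deciding or adjudicating role.

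**2. Reproducing the design.** Inputs from Sample Size: p0 = 0.30, p1 = 0.60, one-sided 5%, power 80%, rules 3/8 and 10/24. The chance of declaring the device effective at observed control rate p is

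P(p) = Σ (x = 4 to 8) Bin(x; 8, p) × Pr[Bin(16, p) ≥ 11 − x]

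At p = 0.30:

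| x of 8 | Bin(x; 8, 0.30) | Pr[at least 11 − x of 16] | product |
|---|---|---|---|
| 4 | 0.1361 | 0.1753 | 0.0239 |
| 5 | 0.0467 | 0.3402 | 0.0159 |
| 6 | 0.0100 | 0.5501 | 0.0055 |
| 7 | 0.0012 | 0.7541 | 0.0009 |
| 8 | 0.0001 | 0.9006 | 0.0001 |

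The unrounded sum is 0.0462. The same formula at p = 0.60 gives 0.8063. A search over two-stage designs with up to 30 patients returns 3/8 and 10/24 as the optimal plan. The stated sample size, level and power are therefore correct; the point concerns whose rating enters the counts.

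**3. Effect of net optimism (illustration).** Assume a true control rate of 0.30 and that a share f of uncontrolled lesions is rated stable, with no errors the other way. The observed rate is then p = 0.30 + 0.70f.

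| f | p | P(declare effective) |
|---|---|---|
| 0 | 0.300 | 4.6% |
| 5% | 0.335 | 9.2% |
| 10% | 0.370 | 16.0% |
| 15% | 0.405 | 24.9% |
| 20% | 0.440 | 35.5% |

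The design has little slack: 0.05 − 0.0462 = 0.0038.

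**4. Errors in both directions.** If a share h of truly controlled lesions is also rated not controlled, the observed rate is 0.30(1 − h) + 0.70f. It stays at 0.30 when 0.30h = 0.70f. At f = 5% this needs h = 0.035/0.30 = 11.7%. The inflation therefore depends on the net error, not on f alone.

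**5. How often step 1 hangs on one patient.** At p = 0.30 the chance of exactly 3 of 8 is 56 × 0.30³ × 0.70⁵ = 0.254. In about a quarter of such trials, one changed rating would open step 2.

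**6. Effect of changing the rater.** The rules do not depend on who rates. With the committee's classification as input, 8, 24, 3, 10, the exact level of 0.0462 and the power of 0.8063 all stand.

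**The case against.** The strongest reply is that an investigator-rated decision with an independent reading reported beside it is a coherent choice for a trial described as exploratory. Much of that reply stands.

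- A reader might infer that the committee never touches the primary result. The text does not support this. Its rate and interval are reported, Table 1 places its evaluation under primary outcomes, and with 24 patients anyone can convert its rate into a count and compare it with 10. What is missing is a role in the decision and a rule for disagreement.
- A reader might infer that the committee is the only protection against bias. Preparation and Treatment of Lesions also ties the rating to lesion measurements, colorimetry and photographs, which limits judgement without removing it.
- It is tempting to say that the investigator delivers the treatment and rates with the cut-offs in mind. No section says so; both are inferences from an open, single-centre study.
- The inflation figures assume that all errors favour the device, and the comparison treats the committee as free of error. The documents do not say what the committee is blinded to, and the Discussion's caveat about comparing photographs applies to it as well. Moving the decision is not shown to restore exactly 4.6%.
- Passing step 1 only opens further enrolment; 11 of 24 are still needed, and the Discussion plans a randomized trial after a positive result.

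None of this explains why a committee introduced to limit investigator bias has no part in the decision most exposed to it.

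**Conclusion.** The point holds as a mismatch between the stated purpose of the committee and the rule that answers the main objective. It is explicit for step 1 and follows for step 2 because the count is cumulative. The sections also disagree on the assessor: Sample Size names none, Table 1 names both, and Statistical Methods names the investigator.

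If the investigator is on balance optimistic, the false-positive rate exceeds 4.6%: 9.2% at f = 5% and 16.0% at f = 10%, with true control of 30% and one-directional error. These figures show sensitivity. They do not estimate this trial's error, because the documents give no misrating rate, and they should not be read as showing that the 5% level is in fact broken.

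This should be fixed, and the improvement is cheap. It does not invalidate the design: the sample size, cut-offs, level and power are correct and both ratings are reported.

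**What to change.** - In Statistical Methods, apply both rejection rules (3 or fewer of 8, 10 or fewer of 24) to the independent committee's 3-month classification.
- Have the committee read the first 8 patients' photographs before the step 1 decision.
- Keep the investigator's rate and 95% confidence interval as a supportive result, and report the number of patients on whom the two ratings disagree.
- Make Table 1, Sample Size, Implementation and Blinding, and Statistical Methods name the same assessor for the primary decision.

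**Cost.** A sentence in Statistical Methods, matching wording in the other sections, and an earlier committee reading of 8 photograph sets. Table 2 already schedules the photographs and the committee already rates at 3 months. No patients are added and no cut-off changes. The small downside is that the committee sees photographs only, so the in-person rating becomes a sensitivity result.

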### Ethical Considerations

The trial is conducted in accordance with principles enunciated in the Declaration of Helsinki, as well as International Council for Harmonisation guidelines and article L1121-4 of the French Health Code. The study protocol has been submitted for review and approval by the French Ethics Committee (2018-68) and the French National Agency for the Safety of Medicines and Health Products (2018-A01873-52 and 2018-002604-13). The trial was registered at ClinicalTrials.gov [NCT03713203]. The investigator must ensure that subjects are informed clearly and fully about the purpose, potential risks, and other critical issues regarding clinical studies in which they volunteer to participate. Freely given written informed consent must be obtained from each subject prior to clinical study participation, including informed consent for any screening procedures conducted to establish subject eligibility for the study. The rights, safety, and well-being of the subjects are the most important considerations and should prevail over interests of science and society.

### Patient Confidentiality and Involvement

Patients or the public were not involved in the conceptualization or carrying out of this research. Concerning treatment of personal data, this study is in compliance with the French methodology of reference (MR0001), which is a simplified declaration of data from medical research to the French National Data Protection Authority. The only persons authorized to access data and modify files generated by the study will be persons directly involved in the study. The participants will have access to the data and be able to modify them at any moment through one of the referring investigators of the study. The sponsor affirms the patient’s right to protection against invasion of privacy.

## Results

The first patient was included in September 2019. Evaluation of disease control in the first 8 patients will determine the study's continuation (early 2020). The final visit of the last patient is expected to August 2022. Analysis of the results is scheduled for the end of 2022, and results are expected to be published at the beginning of 2023.

## Discussion

PDT using 5-aminolevulinic acid has been employed sporadically to treat EMPV even if it is not the common treatment of this pathology [15,16]. MAL-PDT is a relatively simple procedure to treat large and multiple lesions and can be repeated without functional or cosmetics effects. This clinical trial is the only trial registered on ClinicalTrials.gov that investigates the efficacy and safety of PDT in EMPV. But its boundaries are that disease evolution is difficult to evaluate because symptom improvement is based on a medical opinion by comparison of photographs and the limitation of the penetration of MAL at a depth of around 2 to 3 mm for a wavelength of 630 nm according to the thickness of the lesions. In case of positive results, a randomized trial comparing PDT with imiquimod will be performed.

## Abbreviations

5-ALA: 5-aminolevulinic acid
DLQI: Dermatology Life Quality Index
EMPV: extramammary Paget disease of the vulva
FSFI: Female Sexual Functioning Index
HADS: Hospital Anxiety and Depression Scale
LEF: light-emitting fabric
MAL: methyl aminolevulinate
PDT: photodynamic therapy
PpIX: protoporphyrin IX
PS: photosensitizing molecule
SF-36: 36-item Short Form Health Survey
UMBD: Unit of Methodology, Biostatistics and Data Management
